## Abstract

**Background:**

In-centre nocturnal haemodialysis (INHD) offers extended-hours haemodialysis, 6 to 8 h thrice-weekly overnight, with the support of dialysis specialist nurses. There is increasing observational data demonstrating potential benefits of INHD on health-related quality of life (HRQoL). There is a lack of randomised controlled trial (RCT) data to confirm these benefits and assess safety.

**Methods:**

The NightLife study is a pragmatic, two-arm, multicentre RCT comparing the impact of 6 months INHD to conventional haemodialysis (thrice-weekly daytime in-centre haemodialysis, 3.5–5 h per session). The primary outcome is the total score from the Kidney Disease Quality of Life tool at 6 months. Secondary outcomes include sleep and cognitive function, measures of safety, adherence to dialysis and impact on clinical parameters. There is an embedded Process Evaluation to assess implementation, health economic modelling and a QuinteT Recruitment Intervention to understand factors that influence recruitment and retention. Adults (≥ 18 years old) who have been established on haemodialysis for > 3 months are eligible to participate.

**Discussion:**

There are 68,000 adults in the UK that need kidney replacement therapy (KRT), with in-centre haemodialysis the treatment modality for over a third of cases. HRQoL is an independent predictor of hospitalisation and mortality in individuals on maintenance dialysis. Haemodialysis is associated with poor HRQoL in comparison to the general population. INHD has the potential to improve HRQoL. Vigorous RCT evidence of effectiveness is lacking. The NightLife study is an essential step in the understanding of dialysis therapies and will guide patient-centred decisions regarding KRT in the future.

**Trial registration:**

Trial registration number: ISRCTN87042063. Registered: 14/07/2020.

## Introduction

### Background and rationale {6a}

Nearly 70,000 adults in the UK receive kidney replacement therapy (KRT) for end-stage kidney disease (ESKD) [1]. Haemodialysis accounts for over a third of KRT treatment in the UK [1] and 89% of all dialysis worldwide [2]. Despite its value as a life-saving treatment in individuals unable to receive or awaiting kidney transplantation, individuals receiving maintenance haemodialysis have poorer health-related quality of life (HRQoL) than the non-dialysis population, which associates significantly with adverse outcomes, such as hospitalisation and mortality [3–5], and increased co-morbidity, including frailty, reduced physical function and depression [5, 6].

The reasons for poor HRQoL amongst the haemodialysis population are multifactorial and reflect the complex interplay between the constructs of the biopsychosocial model of health [7]. For instance, individuals with kidney failure experience substantial symptom burden, must adjust and cope with living with a challenging chronic illness and are restricted in their time, travel and work [8–10]. Extrapolate this to a societal level, kidney failure and haemodialysis exerts significant strain on the health economy [11].

The individual burden of living with ESKD is compounded by dialysis treatment regimens. The majority of haemodialysis care takes place ‘in-centre’ at a hospital-based or satellite haemodialysis unit [1]. In-centre haemodialysis treatment regimens are rigid; patients must attend thrice-weekly (typically either Monday, Wednesday and Friday, or Tuesday, Thursday and Saturday) with treatment times limited to 3.5 to 5 h per session. This is not at the convenience for the individual, but rather suits the service capacity requirements and managing patient numbers, whilst providing an adequate prescription of dialysis [12].

Individuals receiving haemodialysis within their home experience better quality of life and long-term clinical outcomes in comparison to in-centre haemodialysis [13, 14]. Home haemodialysis offers individuals flexibility regarding the length of dialysis sessions, time of day that treatment takes place and frequency of their treatment. Consequently, individuals can dialyse for longer, mimicking native kidney function to a greater extent compared to in-centre regimens, but with greater autonomy over the schedule. However, home haemodialysis is only utilised by approximately 2% of the UK KRT population [1]; there are considerable professional, patient and societal-related barriers to expanding home haemodialysis services [15, 16]. Alternative haemodialysis regimens are needed to address the dichotomy between in-centre and home haemodialysis therapies.

In-centre nocturnal haemodialysis (INHD) is an alternative regimen whereby individuals have the opportunity to dialyse overnight at a hospital-based or satellite dialysis unit, for 6 to 8 h per session. This increases the total weekly dialysis time to 18 to 24 h, a substantial increase compared to the typical 12 h of daytime in-centre haemodialysis, without impinging on dialysis-free time during the day. There is a growing body of evidence from observational data demonstrating that INHD is associated with improvements in HRQoL [17–20], dialysis adequacy [20–22], surrogates for cardiovascular health [23], survival [21, 24] and clinical parameters (e.g. anaemia and markers of renal bone disease) [17, 21–25]. It is probable that the reason for these observed benefits are due to both the increased dialysis dose and the overnight scheduling, which essentially increases the amount of usable dialysis-free time in comparison to usual in-centre daytime haemodialysis [26]. The extrapolation of these observational findings to the haemodialysis population are limited by significant sources of bias, in particular, selection bias and lack of randomisation, short follow-up period, small sample sizes and inadequate study power.

There have been three key randomised clinical trials (RCTs) evaluating the impact of extended-hours nocturnal haemodialysis in comparison to standard care (in-centre daytime haemodialysis) on HRQoL: the Alberta trial [27], the Frequent Haemodialysis Network (FHN) Nocturnal Trial [28] and the ACTIVE dialysis trial [29]. Disappointingly, all three RCTs did not show a statistically significant improvement in HRQoL with extended-hours nocturnal haemodialysis. Furthermore, the FHN Nocturnal trial demonstrated that allocation to the intervention hastened residual kidney function decline in comparison to the control [30] and a trend towards increased vascular access events with extended-hours nocturnal haemodialysis [28], although this did not reach statistical significance and synthesised data from all three trials indicated there was no difference in vascular access events between intervention and control [31].

These findings need to be interpreted with caution when considering their relevance to INHD. All three RCTs provided a haemodialysis prescription which may be considered *intensive* (i.e. increased duration *and* frequency of haemodialysis) rather than just *extended:* the ACTIVE dialysis trial aimed to achieve ≥ 24 h of haemodialysis a week across a minimum of three dialysis sessions [29]; the FHN Nocturnal Trial intervention involved ≥ 6 h of haemodialysis six times a week [28]; and the Alberta trial intervention required ≥ 6 h of haemodialysis five to six times a week [27]. In all three RCTs, the majority of the nocturnal haemodialysis was performed at home; when only 2% of the UK KRT population utilise home haemodialysis, the applicability of the findings to the usual haemodialysis population is limited.

There is an absence of RCT data dedicated to evaluating the potential benefits and safety of thrice-weekly extended-hours INHD in a UK population. Without robust evidence, expansion of alternative in-centre haemodialysis regimens is restricted. This will be addressed by the NightLife study, a pragmatic multicentre RCT to evaluate the impact of INHD on HRQoL, clinical and cost-effectiveness, and safety in comparison to standard in-centre daytime haemodialysis.

### Aim and objectives {7}

The overall aim of the NightLife study is to test the clinical and cost-effectiveness of 6 months of thrice-weekly, extended-hours (6 to 8 h) INHD compared to standard care haemodialysis (thrice-weekly, 3.5 to 5 h of in-centre haemodialysis during the day) for adults requiring maintenance haemodialysis. This will be achieved with the following objectives:To determine the willingness and ability to recruit and randomise individuals to thrice-weekly, extended-hours INHD.To measure the effect of 6 months of extended-hours INHD compared with daytime haemodialysis on quality of life.To measure the effect of 6 months of extended-hours INHD compared with daytime haemodialysis on sleep, fatigue, dialysis recovery, cognitive function, clinical parameters and dialysis adequacy and safety (including residual kidney function and vascular access complications).To assess feasibility and acceptability of extended-hours INHD to individuals receiving long-term in-centre haemodialysis, their family and care givers, and staff, in order to identify contextual factors that influence the implementation of INHD.To evaluate the cost-effectiveness of 6 months of extended-hours INHD compared with daytime haemodialysis from a health and social care perspective.To understand and address issues that undermine recruitment and retention in the NightLife study.

### Trial design {8}

NightLife is a superiority study delivered as a two-arm, parallel, pragmatic, multicentre RCT. There is an embedded process evaluation, to assess the study’s processes and intervention implementation, and cost-effectiveness analysis. An integrated QuinteT recruitment intervention (QRI) will study attitudes towards recruitment and equipoise [32]. An overview of the NightLife study is demonstrated in Fig. 1.

**Fig. 1 Fig1:**
[figure not shown]
Overview of the NightLife study: the main randomised controlled trial, embedded Process Evaluation to provide a formative evaluation of study processed and intervention implementation, and the QuinteT Recruitment Intervention to optimise recruitment practices and maintain clinical equipoise in study discussions

## Methods: participants, interventions and outcomes

### Study setting {9}

The NightLife study will take place across approximately 18 participating dialysis units, from within the NHS and commercial providers across the UK. Participating dialysis units are eligible from any type of NHS Trust and in any location across the UK providing they have a research ethics department and can deliver the required research activities (i.e. recruitment and data collection) and clinical service provision (i.e. provide an existing or new INHD service). The list of participating sites is available on the NightLife study clinical trials registration page (ISRCTN87042063).

### Eligibility criteria {10}

The eligibility criteria for the main RCT, embedded process evaluation and QRI are reported in Table 1.

**Table 1 Tab1:** Eligibility criteria for the NightLife study

**Workstream 1 (main randomised controlled trial)**
Inclusion criteria:
• Adults (≥ 18 years);
• End-stage kidney failure receiving thrice-weekly in-centre haemodialysis for at least 3 months
• Able to provide written informed consent;
• Able participate fully in follow-up
Exclusion criteria:
• Currently receiving in-centre nocturnal haemodialysis;
• < 3 months since stopping extended daytime dialysis or in-centre nocturnal haemodialysis;
• Extended-hours haemodialysis is clinically indicated (e.g. calciphylaxis, pregnancy)
• Scheduled living-donor transplant in the next 6 months;
• Plans to change dialysis modality in the next 6 months;
• Life expectancy < 6 months;
• Current participation in an interventional trial with conflicting therapies or primary outcome
**Workstream 2 (Process Evaluation)**
Staff inclusion criteria
• Clinical and non-clinical staff working at haemodialysis units participating in the NightLife study;
• Adults (≥ 18 years);
• Ability to give written informed consent;
• Ability and willingness to participate fully in the observations and interviews
Relative/visitor inclusion criteria
• Relatives or visitors accompanying patients (that fulfil workstream 1 eligibility criteria) to haemodialysis sessions;
• Adults (age ≥ 18 years);
• Ability to give written informed consent;
• Ability and willingness to participate fully in the observations and interviews
**Workstream 3 (QuinteT recruitment intervention)**
Staff inclusion criteria
• Clinical and non-clinical staff working involved in overseeing or recruiting to the NightLife study;
• Adults (≥ 18 years);
• Ability to give informed consent

### Who will take informed consent? {26a}

Informed consent will be received by members of the research team (research nurses and clinicians) trained in Good Clinical Practice. Recruitment and informed consent will take place on the dialysis units during potential participants’ usual haemodialysis sessions.

### Additional consent provisions for collection and use of participant data and biological specimens {26b}

Informed consent includes access to medical records and linkage of research data to routine health data relevant to study follow-up. This trial does not involve collecting biological specimens for storage. Separate informed consent is required for the main RCT, embedded process evaluation and integrated QRI. Participation to the main RCT is not required for an individual to join the process evaluation or QRI.

There is an optional cardiac magnetic resonance imaging sub-study for participants joining the main RCT, for which additional informed consent is required. This sub-study protocol will be published separately and is not detailed in this manuscript.

### Explanation for the choice of comparators {6b}

The control group is the typical haemodialysis regimen prescribed in routine nephrology clinical practice: in-centre day time haemodialysis. The intervention is the alternative regimen of thrice-weekly extended-hours INHD, which currently is not widely available within the NHS but has been associated with a number of potential benefits.

### Intervention description {11a}

Participants allocated to the intervention group will receive thrice-weekly, extended-hours (6 to 8 h) INHD for 6 months. The participants allocated to the control arm will continue with thrice-weekly, standard-hour (3.5 to 5 h) in-centre daytime haemodialysis. All other aspects of dialysis care will remain the same.

### Criteria for discontinuing or modifying allocated interventions {11b}

Participants may withdraw from complying with the allocated study treatment arm and/or providing data to the study, at any time, for any reason without affecting their usual care. Should a participant wish to withdraw from receiving their allocated study treatment, efforts will be made to continue to obtain follow-up data, with their permission. Participants do not have to give a reason for withdrawal; however, if they do provide a reason for leaving the study, this will be recorded.

The clinical team and/or investigators may discontinue a participant from the study at any time if considered necessary, e.g. based on symptoms and blood test results.

### Strategies to improve adherence to interventions {11c}

The integrated QRI aims to enhance retention to the NightLife study, as outlined in ‘Recruitment {15}’ below.

### Relevant concomitant care permitted or prohibited during the trial {11d}

All other aspects of dialysis care will remain the same during participation in the NightLife study.

### Provisions for post-trial care {30}

At the end of the 6-month study period, participants allocated to the control arm will have the option of switching to INHD as per capacity of local clinical service. Similarly, participants allocated to INHD have the option to remain on this haemodialysis regimen or return to usual daytime haemodialysis.

### Outcomes {12}

#### Primary outcome measure

The primary outcome is the Kidney Disease Quality of Life (KDQoL) total score measured over 6 months. The KDQoL is a kidney disease-specific measure of HRQoL and has been shown to have reliability and construct validity amongst dialysis patients [33]. The KDQoL is available in different formats; the KDQoL Short Form (KDQoL-SF) questionnaire is being used for the NightLife study. The KDQoL-SF questionnaire includes the generic Short Form-36 as its core with an additional 43 kidney disease-targeted items. The primary outcome (KDQoL total score) is calculated from a subset of data collected in the KDQoL-SF questionnaire.

The KDQoL incorporates four domains: physical component summary score (PCS), mental component summary score (MCS), kidney summary score (KSS) and the kidney disease component summary score (KDCS). The results for each of the dimensions are all generated from the data collected in the KDQoL-SF questionnaire. As well as being a sensitive measure of quality of life, each 1-point improvement in the PCS is associated with reductions in both the relative risk of death and hospitalisation by 2% [34]. Similarly, a 1-point improvement in MCS has been associated with a relative risk reduction for death of 2% and for hospitalisation by 1% [34]. Given that there is an almost linear relationship between lower score and increased hospitalisation and mortality [35], a 5-point difference over 6 months in KDQoL physical score would associate with a clinically significant 5–10% reduction. This 5-point difference equates to a standardised difference of 0.26. The domains of the KDQoL-SF, alongside hospitalisation and mortality, have all been highlighted by the Standardised Outcomes in Nephrology (SONG-HD) initiative as priority outcomes [36]; thus, the KDQoL measures what is most important to individuals requiring maintenance haemodialysis.

#### Secondary outcome measures

The secondary outcome measures will further explore quality of life; evaluate sleep, dialysis recovery and cognitive function; assess safety of the intervention and impact on clinical parameters; and determine adherence to the intervention. The secondary outcome measures, assessment tools and follow-up time points (after baseline data collection) are reported in Table 2.

**Table 2 Tab2:** Secondary outcome measures for Workstream 1 (main randomised controlled trial)

Secondary outcome measures	Follow-up
**Patient reported outcome measures**	
KDQoL total score	1, 3 and 6 months
KDQoL domains: Physical Component Summary Score (PCS), Mental Component Summary Score (MCS), Kidney Summary Score (KSS), Kidney Disease Component Summary Score (KDCS)	6 months
EuroQol EQ-5D-5L: will be used to determine health state descriptions for the five components (mobility, self-care, usual activities, pain/discomfort, anxiety/depression) combined with health-related quality of life index scores to generate quality-adjusted life year (QALY) profiles for the cost-effectiveness analysis	1, 3 and 6 months
The SONG-HD fatigue score to evaluate fatigue experience by individuals on long-term dialysis	1, 3 and 6 months
Pittsburgh Sleep Quality Index (PSQI); a validated tool to assess sleep quality in people on dialysis and the association between sleep and lower health-related quality of life	1, 3 and 6 months
Time to recover in minutes after dialysis; a simple, reliable and sensitive validated tool	1, 3 and 6 months

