### Participant timeline {13}

Overview of participant timeline and schedule of events is summarised in Fig. 1. The schedule of enrolment, randomisation, assessments and follow-up are summarised in Table 3.

**Table 3 Tab3:** The schedule of enrolment, randomisation, assessments and follow-up

Procedure	Screening	Baseline	1 month	2 months	3 months	4 months	5 months	6 months	3 years
Review eligibility criteria	X	X							
Written informed consent		X							
Demographic data and medical history		X							
Questionnaires: KDQoL, EQ-5D-5L, PSQI, SONG-HD, TTR		X	X		X			X	
MoCA		X			X			X	
Baseline health economics questionnaire		X							
Randomisation		X							
Intradialytic urine collection and paired blood samples*		X						X	
Serum beta-2 microglobulin*		X	X	X	X	X	X	X	
Resource use and expenditure questionnaire			X		X			X	
Routine clinical data^◊^ including adherence, dialysis adequacy, blood pressure and monthly blood results		X	X	X	X	X	X	X	
Capture of routine clinical data and resource usage (UKRR, SRR, HES, ONS, ISD)									X

*Blood samples drawn at the same time as routine clinical testing. ^◊^Routinely collected data on all dialysis units

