#### Plans to promote participant retention and complete follow-up {18b}

Study participation on the allocated treatment arm is 6 months. The baseline visit and all follow-up appointments are completed during usual routine haemodialysis appointments. There is the option for quality of life questionnaire data to be completed over the phone if more convenient to the participant. After baseline, the follow-up visits occur at 1, 3 and 6 months. Irrespective of KRT modality after study participation, capture of routine clinical data will take place on the 3-year anniversary of the last participant last visit.

For participants that leave their allocated treatment intervention (i.e. permanent crossovers), permission will be sought to continue to collect follow-up data. Some data may not be available due to death, kidney transplantation and voluntary withdrawal (these losses have been taken into consideration for the sample size calculation) or lack of completion of individual data items. Where possible, the reasons for missing data will be ascertained and reported. Although every effort will be made to minimise crossovers from both treatment arms, the numbers, direction and reasons for participants moving between arms will be recorded and reported in line with CONSORT (Consolidated Standards of Reporting Trials) guidance.

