## Statistical methods

### Statistical methods for primary and secondary outcomes {20a}

#### Primary outcomes

The primary outcome will compare the KDQoL composite score over 6 months between the intervention and control. The primary outcome analysis will be conducted using a modified intention to treat with participants with at least one post baseline measurement of KDQoL analysed in the groups to which they were randomly allocated, regardless of haemodialysis schedule they actually received. The KDQoL total score over 6 months (i.e. 1, 3 and 6 months) will be compared between the treatment arms using a repeated measures mixed linear regression model with participant as a random effect to account for repeated measures over time. The model will be adjusted for a treatment group, minimisation factors (haemodialysis unit and age) with haemodialysis unit as a random effect and baseline KDQoL total score. Treatment comparison estimates will be presented as adjusted mean difference and 95% confidence intervals.

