#### Secondary outcomes

The secondary outcomes will be analysed using linear regression for single point in time continuous outcome measures; repeated measures mixed linear regression model for secondary outcomes measured repeatedly over time; and logistic regression for binary measures. All analyses will be adjusted for baseline value and the minimisation factors (haemodialysis unit and age). The number of deaths and cardiovascular events expected is relatively low; therefore, formal time to event analyses will not be conducted. Kaplan–Meier will be presented to describe the relationship between these events and treatment.

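### The four KDQoL domain scores are listed at 6 months only although the questionnaire yields them at 1, 3 and 6 months: a minor efficiency and alignment point

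*Protocol article*

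**What the plan says.** In Table 2, the patient-reported block opens with the total score, "KDQoL total score 1, 3 and 6 months". The next row covers the four domains: it begins "KDQoL domains: Physical Component Summary Score (PCS), Mental Component Summary Score (MCS" and ends "Kidney Disease Component Summary Score (KDCS) 6 months". The other questionnaire scores in that block (EQ-5D-5L, SONG-HD fatigue, PSQI and recovery time) are all listed at 1, 3 and 6 months. The domains alone are not, and no reason is given.

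Table 3 schedules the row "Questionnaires: KDQoL, EQ-5D-5L, PSQI, SONG-HD, TTR" at baseline, 1, 3 and 6 months. Section {18b} agrees: "After baseline, the follow-up visits occur at 1, 3 and 6 months". On the domains, the primary outcome text in section {12} says: "The results for each of the dimensions are all generated from the data collected in the KDQoL-SF questionnaire".

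For the analysis, section {20a} states: "The KDQoL total score over 6 months (i.e. 1, 3 and 6 months) will be compared between the treatment arms", using a mixed model with participant as a random effect. For secondary outcomes it prescribes "linear regression for single point in time continuous outcome measures" and a mixed model for outcomes measured repeatedly.

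The clinical rationale in section {12} is built on a 5-point difference in the KDQoL physical score over 6 months, equated to the standardised difference of 0.26.

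**The concern.** Domain scores will exist at every questionnaire visit, yet the listed analysis uses one visit. Three things follow.

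- **Time frame.** The total score is summarised over three visits and the domains at one. The physical score, whose target is framed over 6 months, has no listed analysis on that time frame.
- **Data used.** A regression on the month-6 score alone drops anyone without that score unless it is imputed. The primary analysis keeps anyone with at least one post-baseline score. The plan allows for 15% attrition, and section {15} itself worries that control participants may leave more often and report lower quality of life.
- **Precision.** Earlier scores that could narrow the intervals are set aside.

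What is at stake is the precision and comparability of secondary results, not the primary conclusion.

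**Working it through.** **Inputs.** From section {14}: standardised difference 0.26, baseline correlation 0.78, 90% power, 5% type I error (two-sided assumed), 252 evaluable, 15% attrition. From section {16a}: allocation 1:1.33. Assumed: equal correlation between all visits, and the total score's correlation for each domain, because the article gives no domain correlations.

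**The plan's own figure.** Adjusting one follow-up score for baseline leaves a variance factor of 1 − 0.78² = 0.392.
- At 1:1.33, control n = (1 + 1/1.33) × (1.960 + 1.282)² × 0.392 / 0.26², which rounds up to 107. Intervention n is 143, total 250.
- At 1:1 the same formula gives 122 + 122 = 244.

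The stated 252 is reproduced closely at the planned ratio. It rests on the total score, so the domain entry does not touch it.

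**One visit against the mean of three.** For the mean of m follow-ups adjusted for baseline, the variance factor is (1 + (m − 1)ρ)/m − ρ².
- m = 1: 0.392.
- m = 3, ρ = 0.78: (1 + 1.56)/3 − 0.608 = 0.245. The ratio is 0.625, so the variance is 37% lower and the standard error 21% smaller (√0.625 = 0.79).
- If follow-up visits correlate at 0.86 with each other and 0.78 with baseline: (1 + 1.72)/3 − 0.608 = 0.298. The ratio is 0.762, so the standard error is 13% smaller.
- With a common ρ from 0.5 to 0.85, the variance reduction runs from 44% to 36%.

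**What this means for power** (126 per arm, ρ = 0.78):

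| Effect over time | Contrast | Power |
|---|---|---|
| 0.26 at month 6 | 6 months only | 91% |
| Constant 0.26 | Mean of three visits | 98.6% |
| Linear growth to 0.26 at month 6 | Mean of three visits | about 64% |

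In the last row the average effect is 0.26 × (1/6 + 1/2 + 1)/3 = 0.144. Averaging is therefore no improvement in itself; it depends on the shape of the effect.

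**Dropout.** Simulated trials of 150:200 with exchangeable correlation 0.78 and a true 6-month effect of 0.26 had about 16% lost before month 6. Loss depended on the 3-month score and was heavier in control (assumed).
- Unimputed 6-month regression: 0.241, about 7% low.
- The 6-month contrast from the repeated-measures model: 0.261 with a constant effect and 0.260 with a growing one.

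In a comparable scenario (20% loss in control, 8% in intervention, 1,500 trials), unimputed regression gave 0.240. The same regression after multiple imputation from the 1- and 3-month scores gave 0.261. The standard error was 0.074, so the unimputed bias was about a quarter of it (0.020/0.074 = 0.27).

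**The case against.** The trial tests 6 months of treatment, so the end-of-treatment visit is a defensible choice for supportive scores. That stands: the entry is not an error.

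A reader might infer that the domains are there to explain the total score, so that a different time frame defeats their purpose. The article does not say this; section {12} says only that secondary outcomes further explore quality of life. The total score is also a secondary outcome at 1, 3 and 6 months, so a matching 6-month total-score comparison may be available. The abstract even places the primary outcome at 6 months, although sections {12}, {14} and {20a} all say over 6 months. That wording should be reconciled, but it does not change the specified analysis.

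A reader might also infer that the domain results will be biased by dropout. That goes too far. Section {20c} prescribes multiple imputation when at least 5% of participants lack a post-baseline KDQoL score, and planned attrition is 15%. If the rule covers the domains and uses the earlier scores, the simulated bias disappears. The article does not say whether it does, and the detail may properly sit in the SAP. The 7% also depends on an assumed dropout pattern.

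The 21% figure compares two different contrasts and is not a gain for the 6-month contrast. With complete data and visit-specific effects, the mixed model gives essentially the precision of the single-visit regression.

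Finally, the single-visit regression is implied by reading Table 2 with section {20a}; it is not stated for the domains by name. What remains is that the table entry restricts the domains, unlike every other score in its block, without a reason.

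**Conclusion.** The point holds as a minor matter of efficiency and alignment. Table 2 sets the domains at one visit when three are collected, which by the article's rule implies a different model and time frame from the total score. No stated sample size, power or type I error is affected.

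The benefit of change has two parts. The 6-month contrast would use the earlier scores of participants who miss month 6. This protects against dropout related to those scores wherever imputation is not applied to the domains or does not use them. An added over-6-months contrast would match the primary outcome and the physical-score rationale. Its standard error would be about 13 to 21% smaller, on the assumptions of a roughly constant effect and domain correlations near 0.78. If the effect builds over time, that contrast has less power than the 6-month one, so it should be an addition and not a replacement.

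**What to change.** In Table 2, change the follow-up entry for PCS, MCS, KSS and KDCS to 1, 3 and 6 months. Analyse each domain with the total score's repeated-measures model, adjusted for that domain's baseline score and with a visit-by-treatment term. Keep the 6-month contrast as now listed and add the over-6-months contrast to match the primary outcome. If the sponsor prefers 6 months only, state the reason.

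The cost is one table entry, a line in the SAP and reuse of existing model code. No new data are needed. The small downside is one more secondary contrast per domain.
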